### Study design

PROSPER will be conducted under ‘real-world’ clinical practice conditions. Consequently, no changes to the management of HE patients will be made for the purposes of the study.

Once eligible patients have been recruited and consented to participate in the study, two data collection phases will be undertaken (Fig. 1). The first will be a retrospective phase, involving the review of the patients’ medical records and electronic hospital admissions data. Up to 12 months of data prior to study entry will be reviewed and collected. The level and nature of missing data will be assessed and accounted for in the statistical analysis plan, if necessary. The retrospective phase will be followed by a prospective phase, during which data will be collected from all patients either receiving rifaximin-α 550 mg (rifaximin-α 550 mg cohort) or not receiving rifaximin-α 550 mg (control cohort) from the point of study entry. Up to 24 months of data following study entry will be collected and analysed.

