**Fig. 1 Fig1:**
[figure not shown]
Study design

In order to minimise bias and the influence of confounding factors, the study outcomes will be compared between the treatment cohorts in three ways (Fig. 1). The first approach will initially involve the clinical characterisation of the study population, based on retrospective chart review (Fig. 1, comparison 1a), following which outcomes between the cohorts will be compared after adjustment of statistical methods on the basis of the findings from comparison 1a (Fig. 1, comparison 1b). Secondly, for each cohort individually, outcomes pre and post baseline will be compared (Fig. 1, comparisons 2a and 2b). Thirdly, the difference between the two cohorts in pre/post changes will be compared (Fig. 1, comparison 3).

Patients will be eligible to enrol during or following hospitalisation for the qualifying episode of overt HE (Fig. 2; timepoint 1). Patients will also be eligible to enter the study at the time of resolution of the qualifying episode of overt HE (Fig. 2; timepoint 2) or at a follow-up appointment, providing this is within 12 weeks of resolution of the qualifying episode of overt HE (Fig. 2; timepoint 3).

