### Study population

Patients with cirrhosis and HE will be enrolled into PROSPER. The study will employ a limited number of inclusion and exclusion criteria in order to reflect the diversity of patients encountered in clinical practice (Table 1).

**Table 1 Tab1:** Inclusion and exclusion criteria

Inclusion criteria	Exclusion criteria
• Diagnosis of cirrhosis	• West Haven score of ≥2 at study entry
• Age ≥ 18 years	• A mental health disorder that makes HE diagnosis questionable (e.g., dementia, psychosis)
• Enrolment within 12 weeks of resolution of an episode of overt HE associated with a hospital visit	• Prior treatment with rifaximin^a^ within 12 months prior to the qualifying overt HE episode
• Ability to provide informed consent	• Contraindications to the use of rifaximin-α 550 mg, as per the local Summary of Product Characteristics [16, 17]
• Clinical eligibility to receive rifaximin-α 550 mg, in the opinion of the participating physician, regardless of HE treatment actually received	

*HE* hepatic encephalopathy

^a^All types and dose strengths of rifaximin

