### Study assessments

The study’s primary endpoint will be the HE- and liver-related hospitalisation rate and the resulting duration of hospitalisation (number of bed-days). Secondary endpoints will include the rate of all-cause hospitalisation and the resulting duration of hospitalisation (number of bed-days), mortality rate, and the number, duration and severity of HE episodes. Effects of treatment on the underlying liver disease will also be assessed as secondary endpoints using the Child-Turcotte-Pugh score, Model for End-stage Liver Disease (MELD) score or MELD-Na score (a modified MELD score including serum sodium [22]). In addition, the effectiveness of treatment will be assessed by the patient, caregiver and physician, using the Global Evaluation of Treatment Effectiveness (GETE) questionnaire. This consists of the single question ‘*How effective has [your treatment/the treatment] been in controlling [your/the patient’s] HE?*’, which is answered by choosing one of five responses: ‘*Complete control of HE*’, ‘*Marked improvement in HE*’, ‘*Limited improvement in HE*’, ‘*No appreciable change in HE*’ or ‘*Worsening of HE*’.

The safety of treatment with rifaximin-α 550 mg will be evaluated by assessing the frequency and nature of adverse events (AEs) and serious AEs. This will include classification of the severity of AEs and their relationship/causality in relation to medical treatment of HE.

The effects of treatment on health-related QoL will be assessed using the patient-reported Chronic Liver Disease Questionnaire (CLDQ) [23], the patient-reported Euroqol-5 Dimension-5 level (EQ-5D-5L) measure and the caregiver-reported proxy EQ-5D-5L:1 measure [24]. The CLDQ is a 29-item questionnaire assessing a wide range of physical, emotional and psychosocial QoL-related factors during the previous 2 weeks [23]. The EQ-5D-5L and proxy EQ-5D-5L are six-item questionnaires assessing the patient’s mobility, ability to self-care, ability to undertake usual activities, pain/discomfort, anxiety/depression and overall health status on the particular day in question [24].

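### Consent at entry means pre-entry admissions were survived while post-entry ones can be fatal, which pushes comparisons 2a and 2b upward and distorts comparison 3 when underlying case fatality differs between cohorts

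*Protocol article*

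**What the plan says.** The order of events is set in the protocol article under Study design: "Once eligible patients have been recruited and consented to participate in the study, two data collection phases will be undertaken". The first phase looks back ("Up to 12 months of data prior to study entry will be reviewed and collected") and the second looks forward ("Up to 24 months of data following study entry will be collected and analysed"). Table 1 makes the patient's own consent a condition of entry: "Ability to provide informed consent".

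Three comparisons are planned to limit bias and confounding. Comparison 1b sets the cohorts side by side after entry, with adjustment. In 2a and 2b, "for each cohort individually, outcomes pre and post baseline will be compared". In comparison 3, "the difference between the two cohorts in pre/post changes will be compared".

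The primary endpoint is the rate of HE- and liver-related admissions and the bed-days they cause, with no distinction between survived and fatal stays. Deaths are expected after entry, since the secondary endpoints include "mortality rate, and the number, duration and severity of HE episodes". Under Statistical analysis, death enters the count model through an offset for the time a patient could have been admitted.

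**The concern.** A patient who died in hospital before entry could not have consented, so that patient's fatal admission and its bed-days are absent from the retrospective data. The same kind of admission after entry is counted. Comparisons 2a and 2b therefore set survived admissions against survived plus fatal ones. This would remain with windows of equal length, with the qualifying episode removed and with complete records.

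The offset does not reach it. Stopping the clock at death makes the post-entry denominator right, but it neither takes fatal admissions out of the post-entry count nor puts them back before entry.

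At stake is how far the pre/post contrasts can bear the role the article gives them. If the cohorts differ in how often an admission is fatal, for reasons unrelated to the drug, that difference passes into comparison 3 as an apparent difference in the change in admissions.

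**Working it through.** The article gives no figure on this point to reproduce. Its sample size does reproduce (100/0.45 = 222.2; 222.2/0.90 = 246.9, so 247 per cohort and 494 in all) and is unaffected.

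**Assumed inputs** (none is in the article):
- λ, survived HE/liver admissions per year, the same in both windows: 1.0 to 1.7
- m, annual mortality after entry: 15% to 30%, with hazard h = −ln(1 − m), so 0.1625 to 0.3567
- f, share of deaths that occur during an HE/liver admission: 50% to 80%
- length of stay: 15 days if fatal, 10 otherwise

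**Comparisons 2a and 2b, rate, no drug effect.** Post/pre ratio = (λ + h·f)/λ. The product h·f runs from 0.1625 × 0.5 = 0.0813 to 0.3567 × 0.8 = 0.2853.

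| λ | low h·f | high h·f |
|---|---|---|
| 1.0 | 1.0813/1.0 = 1.08 | 1.2853/1.0 = 1.29 |
| 1.7 | 1.7813/1.7 = 1.05 | 1.9853/1.7 = 1.17 |

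**Bed-days.** Ratio = (10λ + 15·h·f)/(10λ) = 1 + 1.5·h·f/λ. Lowest: 1 + 1.5 × 0.0813/1.7 = 1.07. Highest: 1 + 1.5 × 0.2853/1.0 = 1.43.

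**Second route.** Let L be the underlying admission rate and c the case fatality per admission. Among patients who survive to entry the pre-entry rate is L(1 − c); after entry, per unit of person-time, it is L. The ratio is 1/(1 − c): 1.05, 1.11, 1.18 and 1.25 for c = 5%, 10%, 15% and 20%. A simulation with exact person-time and an assumed 1.5 admissions a year gave 1.05, 1.11 and 1.24 for c = 5%, 10% and 20%, so the offset leaves the effect in place.

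**Sensitivity to λ.** If the 45% hospitalised at 12 months in the sample size section is read as a constant rate (an assumption), λ = −ln(0.55) = 0.598, and the ratio runs from 1 + 0.0813/0.598 = 1.14 to 1 + 0.2853/0.598 = 1.48. The main range is not at the high end.

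**Comparison 3.** With no drug effect, the ratio of ratios (rifaximin over control) is (1 − c_control)/(1 − c_rifaximin), where c is underlying case fatality. Equal c gives 1.00. For rifaximin against control, 5% vs 10% gives 0.95, 10% vs 20% gives 0.89, and 10% vs 5% gives 1.06. In the mortality form, 15% (h = 0.1625) on rifaximin against 25% (h = 0.2877) in controls, with the gap unrelated to the drug, gives (1.7 + 0.0813)/(1.7 + 0.1438) = 0.97 at λ = 1.7 and f = 50%, and (1 + 0.1300)/(1 + 0.2301) = 0.92 at λ = 1.0 and f = 80%.

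**The opposing effect.** If the qualifying visit counts as one extra admission in a 12-month pre-entry window, it alone gives λ/(λ + 1), which is 0.50 at λ = 1.0 and 0.60 at λ = 1.5.

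**The case against.** **Net direction.** A reader might infer that the pre/post ratios will end up above 1. The documents do not support that. Table 1 requires a recent overt HE episode with a hospital visit, which loads the pre-entry side and probably outweighs the survivor effect. Within the rifaximin cohort the survivor effect also works against showing benefit. Both points stand, but two opposing distortions of unknown size do not make the contrast sound, and removing the qualifying visit would leave this one fully exposed.

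**Mortality and comparison 3.** A reader might infer that any mortality gap between cohorts distorts comparison 3. It does not. What must match is underlying case fatality. If the drug itself prevents fatal admissions, the resulting fall in admissions is a real effect on the endpoint, and 0.92 to 0.97 would then be signal.

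**Survived admissions as the main analysis.** It is tempting to base 2a, 2b and 3 on survived admissions alone. That selects on an outcome arising after treatment. Suppose the drug leaves L unchanged but halves c from 20% to 10%. With all admissions both cohorts show 1/0.8 = 1.25, so the ratio of ratios is 1.00, as it should be. With survived admissions only, treated patients show 0.9/0.8 = 1.125 and controls 1.00, a false 1.125 against a drug that saves lives. Fatal stays are also genuine resource use, which the study sets out to measure. This objection stands and limits the fix.

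**Straddling stays.** Patients may enrol during the qualifying admission, so a stay begun before entry can end in death after it. The statement about survived admissions therefore holds only for stays that ended before entry.

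**Level of detail.** The article offers only an overview, and the statistical analysis plan is not shown, so it cannot be said that no step exists there. But the article itself fixes the pre/post contrasts, presents them as protection against bias and states how death enters the count model. That treatment of death does not correct the asymmetry.

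**Conclusion.** The point holds in limited form. It follows from the design that stays which ended before entry were survived and that later stays include fatal ones. Its size is assumption throughout: taken alone and with no drug effect, about 1.05 to 1.29 for rates and 1.07 to 1.43 for bed-days in 2a and 2b. Comparison 3 is affected only where underlying case fatality differs between cohorts; the scenarios tried moved it by 3% to 11%, in either direction. Comparison 1b does not use the pre-entry window and is untouched.

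**What to change.** - Flag each post-entry admission as discharged alive or ended in death.
- Assign any stay that straddles entry to one window by a rule fixed in advance.
- For 2a, 2b and 3, report the pre/post contrast twice, with all admissions and with survived admissions only. Show fatal admissions and their bed-days separately, beside mortality.
- Treat a pre/post conclusion as robust only if both versions agree.
- Rest the treatment comparison on 1b with all admissions.

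The cost is wording in the analysis plan and one variable that should be available from the admissions data already being collected. The survived-only version can penalise a drug that lowers case fatality, so it should accompany the all-admissions contrast and not replace it. Non-fatal admissions that cluster shortly before death remain uncorrected.

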**Fig. 2 Fig2:**
[figure not shown]
Timing of entry into study, relative to overt HE episode. HE, hepatic encephalopathy

### Study population

Patients with cirrhosis and HE will be enrolled into PROSPER. The study will employ a limited number of inclusion and exclusion criteria in order to reflect the diversity of patients encountered in clinical practice (Table 1).

**Table 1 Tab1:** Inclusion and exclusion criteria

Inclusion criteria	Exclusion criteria
• Diagnosis of cirrhosis	• West Haven score of ≥2 at study entry
• Age ≥ 18 years	• A mental health disorder that makes HE diagnosis questionable (e.g., dementia, psychosis)
• Enrolment within 12 weeks of resolution of an episode of overt HE associated with a hospital visit	• Prior treatment with rifaximin^a^ within 12 months prior to the qualifying overt HE episode
• Ability to provide informed consent	• Contraindications to the use of rifaximin-α 550 mg, as per the local Summary of Product Characteristics [16, 17]
• Clinical eligibility to receive rifaximin-α 550 mg, in the opinion of the participating physician, regardless of HE treatment actually received	

*HE* hepatic encephalopathy

^a^All types and dose strengths of rifaximin

### Study assessments

The study’s primary endpoint will be the HE- and liver-related hospitalisation rate and the resulting duration of hospitalisation (number of bed-days). Secondary endpoints will include the rate of all-cause hospitalisation and the resulting duration of hospitalisation (number of bed-days), mortality rate, and the number, duration and severity of HE episodes. Effects of treatment on the underlying liver disease will also be assessed as secondary endpoints using the Child-Turcotte-Pugh score, Model for End-stage Liver Disease (MELD) score or MELD-Na score (a modified MELD score including serum sodium [22]). In addition, the effectiveness of treatment will be assessed by the patient, caregiver and physician, using the Global Evaluation of Treatment Effectiveness (GETE) questionnaire. This consists of the single question ‘*How effective has [your treatment/the treatment] been in controlling [your/the patient’s] HE?*’, which is answered by choosing one of five responses: ‘*Complete control of HE*’, ‘*Marked improvement in HE*’, ‘*Limited improvement in HE*’, ‘*No appreciable change in HE*’ or ‘*Worsening of HE*’.

The safety of treatment with rifaximin-α 550 mg will be evaluated by assessing the frequency and nature of adverse events (AEs) and serious AEs. This will include classification of the severity of AEs and their relationship/causality in relation to medical treatment of HE.

The effects of treatment on health-related QoL will be assessed using the patient-reported Chronic Liver Disease Questionnaire (CLDQ) [23], the patient-reported Euroqol-5 Dimension-5 level (EQ-5D-5L) measure and the caregiver-reported proxy EQ-5D-5L:1 measure [24]. The CLDQ is a 29-item questionnaire assessing a wide range of physical, emotional and psychosocial QoL-related factors during the previous 2 weeks [23]. The EQ-5D-5L and proxy EQ-5D-5L are six-item questionnaires assessing the patient’s mobility, ability to self-care, ability to undertake usual activities, pain/discomfort, anxiety/depression and overall health status on the particular day in question [24].

Workplace productivity impairment will be assessed in patients using the Work Productivity and Activity Impairment Questionnaire: General Health V2.0 (WPAI:GH) and in caregivers using the Work Productivity and Activity Impairment Questionnaire: General Health Care Giving V2.0 (WPAI:GH-CG) [25]. These are six-item questionnaires assessing the effects of the patient’s health problems (WPAI:GH), or the effects of caregiving for the patient’s health problems (WPAI:GH-CG), on the individual’s ability to work and perform daily activities. A schedule for these assessments is shown in Table 2.

**Table 2 Tab2:** Schedule of assessments

	Enrolment	1 month^a^	3 months^a^	6 months^a^	12 months^a^	18 months^a^	24 months^a^
Informed consent provided by patient and caregiver (note that caregiver consent is optional for patient study inclusion)	X						
Retrospective chart review (collection of demographic and medical history data)	X						
Ongoing clinical data, including clinical outcomes, laboratory measures, medication dose/schedule, resource utilisation, medication adherence^b^		X	X	X	X	X	X
GETE^c^		X		X			
CLDQ^b^	X				X		X
EQ-5D-5L (patient)^d^	X		X	X	X	X	X
EQ-5D-5L Proxy (caregiver)^d,e^	X		X	X	X	X	X
WPAI (patient)^c^	X		X	X	X	X	X
WPAI (caregiver)^c^	X		X	X	X	X	X

*CLDQ* Chronic Liver Disease Questionnaire, *EQ-5D-5 L* Euroqol-5 Dimension-5 level measure, *GETE* Global Evaluation of Treatment Effectiveness questionnaire, *WPAI* Work Productivity and Activity Impairment questionnaire

^a^Target dates only; flexible depending on patient response

^b^To be collected at all clinic visits but not at fixed time intervals; clinic visits will be scheduled by investigator and patient according to normal management and not defined by study protocol

^c^To be collected at the clinic visit closest to the indicated study date; no additional clinic visits to be scheduled for study participation

^d^To be requested for patient completion via paper submission or online portal or at clinic visit closest to the indicated date; clinic visit may not be required

^e^Australia, UK, Ireland, France and Germany, where the proxy response has been validated

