The neuropsychiatric symptoms of HE are thought to result from elevated blood levels of gut-derived neurotoxins (particularly ammonia), which enter the brain due to the inability of the cirrhotic liver to remove them from the blood [13]. Rifaximin-α 550 mg is a locally acting oral antibiotic that is minimally absorbed in the gut to reduce the effects of intestinal flora, including ammonia-producing species [14]. Its clinical activity may be due to its effects on the metabolic function of gut microbiota, rather than a change in relative bacterial abundance [15]. Rifaximin-α 550 mg is indicated in Europe for the reduction in recurrence of episodes of overt HE in patients aged ≥18 years [16]. In Australia, it has the same indication, but is restricted to where other treatments have failed or are contraindicated [17]. The efficacy of rifaximin-α 550 mg has been confirmed in a randomised controlled trial (RCT), in which rifaximin-α 550 mg twice daily (administered concomitantly with lactulose therapy in approximately 91% of patients) reduced the relative risks of recurrence of overt HE and HE-related hospitalisation by 58% and 50%, respectively, compared with placebo (absolute risk reductions: 24% and 9%, respectively) [18]. In a subsequent 2-year extension study, long-term treatment with rifaximin-α 550 mg (with concomitant lactulose in approximately 90% of patients) provided a continued reduction in the rate of HE-related and all-cause hospitalisation, without an increased rate of adverse events [19].

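### The Child-Turcotte-Pugh score, one of three scores named for effects on the underlying liver disease, includes encephalopathy, so a difference in it can partly reflect HE status and not liver function

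*Protocol article*

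**What the plan says.** Study assessments, in the Protocol article, sets the endpoint: "Effects of treatment on the underlying liver disease will also be assessed as secondary endpoints using the Child-Turcotte-Pugh score". The same sentence goes on to name MELD or, with serum sodium added, MELD-Na. The sentence before it lists HE outcomes as secondary endpoints of their own: "mortality rate, and the number, duration and severity of HE episodes".

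Three other places bear on the point:

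- The Introduction gives the purpose of the treatment: "Rifaximin-α 550 mg is indicated in Europe for the reduction in recurrence of episodes of overt HE".
- Table 1 (Study population) selects on HE status. It requires "Enrolment within 12 weeks of resolution of an episode of overt HE associated with a hospital visit" and excludes patients with "West Haven score of ≥2 at study entry".
- Study design compares the cohorts with each other (comparison 1b). It adds that "for each cohort individually, outcomes pre and post baseline will be compared" (comparisons 2a and 2b), and then compares the pre/post changes between cohorts (comparison 3).

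The article does not list the CTP items. It does not say that the encephalopathy item will be left out or shown separately.

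**The concern.** The article gives HE episodes and the underlying liver disease separate endpoints. CTP does not keep the two apart, because encephalopathy is part of the score. In many cirrhosis studies this would do little harm. Here the treatment under study is meant to change exactly that item.

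Suppose the rifaximin-α cohort has less HE when CTP is scored. Its mean CTP will then be lower even if bilirubin, albumin, INR and ascites are the same in both cohorts. Read as the article labels it, that difference would be reported as an effect on the underlying liver disease, although part or all of it would be the HE effect appearing a second time.

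**Working it through.** **The plan's own figure.** The article gives no figure for this endpoint. Its only design calculation reproduces: 100 events / 0.45 = 222.2; 222.2 / 0.90 = 246.9, rounded up to 247 per cohort; 2 × 247 = 494. CTP does not enter it, so nothing below changes the sample size.

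**Inputs**

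- CTP scoring (assumption: standard definition, not printed in the article): bilirubin, albumin, INR, ascites and encephalopathy, each scored 1 to 3; total 5 to 15; class A 5–6, B 7–9, C 10–15. The encephalopathy item scores 1 for none, 2 for grade 1–2 and 3 for grade 3–4.
- Difference between cohorts in the share of patients with HE at the scoring visit, *d*: assumed 0.05 to 0.24. The upper end borrows the 24% absolute risk reduction in overt HE recurrence that the Introduction reports for the earlier randomised trial. That figure describes recurrence and not presence at a visit, so it is only an illustrative ceiling.

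**Step 1: movement in one patient.** With the other four items fixed, the change in total equals the change in the HE item:

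- none to grade 1–2: 2 − 1 = 1 point
- none to grade 3–4: 3 − 1 = 2 points
- grade 1 to grade 2: 2 − 2 = 0 points

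**Step 2: change of class.** The other four items have 3⁴ = 81 possible profiles. Their sums from 4 to 12 occur 1, 4, 10, 16, 19, 16, 10, 4 and 1 times.

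- HE item 1 versus 2: the class changes when the other items sum to 5 (total 6 versus 7, 4 profiles) or 8 (total 9 versus 10, 19 profiles). 4 + 19 = 23 of 81.
- HE item 1 versus 3: the class changes at sums 4 (1 profile), 5 (4), 7 (16) and 8 (19). 1 + 4 + 16 + 19 = 40 of 81.

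Profiles are counted equally and not weighted by how often patients have them, so these are not patient percentages.

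**Step 3: difference in cohort means.** If *k* is the number of points by which HE raises the item, the mean difference with identical scores on the other four items is *d* × *k*.

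| *d* | *k* = 1 | *k* = 2 |
|---|---|---|
| 0.05 | 0.05 | 0.10 |
| 0.10 | 0.10 | 0.20 |
| 0.20 | 0.20 | 0.40 |
| 0.24 | 0.24 | 0.48 |

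The *k* = 2 column requires that all the excess HE be grade 3–4 at the scoring visit, so 0.48 is the far corner of the range.

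**Step 4: without the item.** In a four-item CTP (range 4 to 12), or in MELD or MELD-Na, this contribution is 0.

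**The case against.** The strongest reply is that the sentence names three scores and two of them have no HE item. This stands. A reader might infer that the endpoint cannot answer its question at all. The document does not support that, because MELD or MELD-Na can answer it.

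Other parts of the case against also stand:

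- **Not every HE benefit registers.** A change between grade 1 and grade 2, the article's own boundary between covert and overt HE, scores zero. Clinical data come from routine visits (Table 2, footnote b), so episodes that start and resolve between visits may leave no trace in CTP. CTP does not count the HE effect a second time in full.
- **The entry rule.** It is tempting to say that excluding West Haven ≥2 at entry biases the cohort comparison. The rule applies to both cohorts, so it does not do so by itself, and comparison 3 removes whatever part of its effect is equal in both. A baseline taken from the chart of the qualifying episode would add a fall on recovery, but the article does not say which CTP value is the baseline.
- **The word 'or'.** A reader might take it as leave to report CTP alone. It may equally reflect which results are available in routine care, and the choice of score can be settled in the full protocol or analysis plan.
- **Familiarity.** HE is a complication of liver disease, and a composite that includes it is a defensible measure of overall severity.

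What remains is the overlap itself. Comparison 3 cancels distortions common to both cohorts, but an effect of treatment on HE is by nature a difference between cohorts and passes through it. Covariate adjustment does not remove it either, since it arises from the composition of the score.

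**Conclusion.** The point holds for CTP only. As a measure of effect on the underlying liver disease in a study of an HE-preventing drug, CTP partly restates HE status. The HE item can move an individual total by 1 to 2 points. Under the assumed 5 to 24 percentage-point difference in HE at scoring, it shifts the difference in means by about 0.05 to 0.48 points.

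The conclusion rests on the standard definitions of the scores, which the article does not print. The mean shift also rests on the assumed prevalence differences, and its actual size cannot be derived from the document. Only this secondary endpoint is concerned. The correction is worth making mainly because it is cheap.

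**What to change.** In Study assessments, state that the conclusion on underlying liver disease rests on MELD or MELD-Na. Where item-level data are available, report CTP without the encephalopathy item as support. Present the full CTP score only as a descriptive measure of overall severity.

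This takes a sentence or two in the endpoint definition. Table 2 already lists laboratory measures among the ongoing data, though not which ones, so the availability of the MELD components should be confirmed. The four-item score is less familiar to readers and may not be computable where charts hold only a total or a class. In those patients the MELD or MELD-Na part of the change still works, provided the laboratory values are on record.

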The rate of all-cause hospitalisation and the resulting duration of hospitalisation will be analysed in the same way as the primary endpoints. Numeric measures (e.g., CLDQ, EQ-5D-5L and GETE scores) will be analysed using a linear regression model, with longitudinal methodology to account for repeated measures, if applicable. Event-based variables and count data (e.g., AEs, HE episodes, mortality) will be analysed using Poisson or negative binomial regression, with offset terms to account for exposure time, length of time eligible to receive hospitalisation and competing risks (e.g., death); analyses will also adjust for underlying differences between cohorts (i.e., confounding factors). Time-to-event methods (e.g., Kaplan Meier analysis) will be used for variables such as time until death. Categorical demographic and clinical characteristics will be presented descriptively as frequency/percentage distribution and compared using a chi-squared test. Continuous demographic and clinical characteristics will be presented descriptively as means with 95% confidence intervals and compared using a Student’s *t*-test.

It is anticipated that additional analyses will include treatment adherence and switching, and the integration of survival data with QoL data, to assess quality-adjusted life-years (QALYs). Other exploratory analyses may also be conducted.

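### The only pre-baseline quality-of-life and WPAI value is taken at enrolment, from the index admission to 12 weeks after resolution, so within-cohort change includes recovery from the HE episode

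*Protocol article*

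**What the plan says.** **Entry window.** The Study design section gives three entry points. The first is around the admission: "Patients will be eligible to enrol during or following hospitalisation for the qualifying episode of overt HE". The second is resolution of the episode. The third is a follow-up appointment, "providing this is within 12 weeks of resolution of the qualifying episode of overt HE". Table 1 repeats the outer limit ("Enrolment within 12 weeks of resolution of an episode of overt HE associated with a hospital visit") and excludes patients with "West Haven score of ≥2 at study entry".

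**Baseline forms.** Table 2 puts the first CLDQ, EQ-5D-5L (patient and proxy) and WPAI (patient and caregiver) at enrolment. The retrospective phase draws on medical records and admissions data, so it supplies no earlier value. The next target dates are 3 months for EQ-5D-5L and WPAI and 12 months for CLDQ, although a footnote also has CLDQ collected at all clinic visits.

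**What the forms ask about.** On the CLDQ: "The CLDQ is a 29-item questionnaire assessing a wide range of physical, emotional and psychosocial QoL-related factors during the previous 2 weeks". EQ-5D-5L asks about health, including "overall health status on the particular day in question". The article gives no recall period for WPAI.

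**Comparisons.** Study outcomes are compared in three ways, with no exception for quality of life. One is described so: "Secondly, for each cohort individually, outcomes pre and post baseline will be compared" (2a, 2b). Comparison 3 is the difference between cohorts in those changes. Under Statistical analysis, numeric measures such as CLDQ and EQ-5D-5L "will be analysed using a linear regression model, with longitudinal methodology to account for repeated measures, if applicable".

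**The concern.** A patient entered during the admission or soon after resolution starts from a low point that would be expected to lift whatever treatment follows. A patient entered near week 12 starts from something closer to a stable state. Both values serve as the same baseline. An improvement within the rifaximin-α cohort then contains an unknown amount of ordinary recovery, and so does any improvement within the control cohort. If the cohorts also differ in how soon after the episode they are enrolled, part of the recovery remains in the between-cohort difference in change. The Statistical analysis section relies on the three-way structure to reduce bias; for these measures, comparisons 2a and 2b do not do so. The endpoints affected are secondary. The hospitalisation endpoint is not touched by this point.

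**Working it through.** **The plan's own figures.** The article states no effect size, SD or power for quality of life. Its sample size rests on hospitalisation events and reproduces: 100 / 0.45 = 222.2; 222.2 / 0.90 = 246.9, so 247 per cohort and 494 overall. The present point does not depend on it.

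**Step 1: what the baseline form can see (documents only).** Let d be days from resolution to the form.
- CLDQ looks back 14 days. For d < 14 it covers 14 − d days before resolution, which includes at least part of the overt episode. For d ≥ 14 it covers none.
- EQ-5D-5L asks about the day. West Haven ≥2 is excluded at entry, so it cannot describe overt HE, but it may describe early convalescence. The same may hold for WPAI.
- A patient entered at 12 weeks has a baseline at day 84. A patient entered at resolution has the first EQ-5D-5L follow-up at about 3 months. Nearly the same point in recovery is baseline for one and follow-up for the other.

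**Step 2: share of CLDQ forms affected (assumption: entry uniform over 0 to 84 days).** 14 / 84 = 17%. The share rises if more patients enter in hospital or at resolution.

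**Step 3: size of the recovery component (assumptions, not in the documents).** Let the deficit at day t after resolution be D·exp(−t/τ) in SD units, with D from 0.3 to 0.8 and τ from 14 to 56 days, and let follow-up be after recovery. The mean deficit for entry uniform over days a to b is

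D·τ·[exp(−a/τ) − exp(−b/τ)] / (b − a).

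Within a cohort (a = 0, b = 84):
- D = 0.5, τ = 28: 0.5 × 28 × (1 − exp(−3)) / 84 = 0.16 SD.
- D = 0.3, τ = 14: 0.05 SD. D = 0.8, τ = 56: 0.41 SD.

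With slow recovery, a 3-month follow-up still carries some deficit, so the gain at that visit would be somewhat smaller.

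**Step 4: comparison 3 (same assumptions).**
- Same entry timing in both cohorts: bias 0.
- One cohort entering in days 0–14, the other over 0–84: 0.11 to 0.38 SD. At D = 0.5, τ = 28 the mean deficits are 0.39 and 0.16, a difference of 0.24 before rounding of the parts.
- One cohort in days 0–42, the other in days 42–84: 0.09 to 0.32 SD (0.20 at D = 0.5, τ = 28).

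**Step 5: a cruder version in EQ-5D units (assumed deficit 0.20 for early entrants, none for later ones).** With 60% and 30% early entrants: 0.12 − 0.06 = 0.06. With 45% and 35%: 0.09 − 0.07 = 0.02. Giving every early entrant the full deficit makes these figures run high.

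**The case against.** Four counter-arguments deserve weight.

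1. **Overt HE has cleared at entry.** A reader might infer that baseline is taken in acute HE. The documents do not support that: West Haven ≥2 is excluded and patients must be able to consent. Only the CLDQ recall period reaches back into the episode. This stands, and it limits the EQ-5D-5L and WPAI argument to early convalescence.

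2. **There is a concurrent control.** Both cohorts recover, share one entry window, and must be clinically eligible for rifaximin-α. Comparison 3 subtracts shared recovery, and comparison 1a is meant to reveal differences for adjustment in 1b. A reader might infer that the between-cohort comparison is biased. That is not shown. It is only not prevented: treatment is unrandomised, visits follow normal management, and prior rifaximin is excluded only for the 12 months before the qualifying episode, so entry timing could be linked to treatment.

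3. **Change from baseline is not named for quality of life.** It follows from the general statement on study outcomes in Study design, not from the model sentence in Statistical analysis, and Fig. 1 is not available here. This is fair, but nothing exempts these measures from the pre/post comparisons.

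4. **Covariates belong in the SAP.** The lack of a covariate list is indeed no finding. But no between-cohort adjustment removes recovery from a within-cohort contrast, and that contrast is stated in the article.

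A reader might also infer that the planned QALYs are materially distorted. Even the high 0.06 gap, with trapezoidal integration over the first 3 months, gives 0.06 × 0.25 / 2 = 0.0075 QALY. The documents do not support making that a concern.

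**Conclusion.** The point holds for within-cohort change. Because the only baseline is tied to enrolment and the entry window spans early convalescence, pre/post change in CLDQ, EQ-5D-5L and WPAI includes recovery from the index episode and does not measure treatment effect. This requires only that these scores improve after an episode. CLDQ is the most exposed.

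For comparison 3 the point is conditional: no bias if time from resolution to enrolment is alike in the cohorts, and bias if it is not. The documents neither show nor rule out a difference.

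The sizes (0.05 to 0.41 SD within a cohort, 0 to 0.38 SD between cohorts across the scenarios) rest on assumed deficits, recovery speeds and entry patterns. They show that the effect need not be negligible; they do not estimate it. No change to sample size follows.

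**What to change.** - Derive days from episode resolution to the baseline form, and report the distribution by cohort. Resolution and enrolment dates are already needed to check eligibility.
- Include this variable as a covariate, or in the propensity score, in the between-cohort quality-of-life and WPAI models.
- Label comparisons 2a and 2b as descriptive for quality of life and WPAI, and say that they include recovery from the index episode.
- Add a sensitivity analysis of pre/post change limited to baseline forms completed at least 2 weeks after resolution.

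The cost is one more model term and some wording. The sensitivity set will be smaller and may select patients differently in the two cohorts, so it should support the main analysis and not replace it. No extra visit, form or patient is needed, and the existing follow-up assessments keep their place in the analysis.
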